## Abstract

**Background:**

There are limited data comparing the oncologic and fertility outcomes of patients with early-stage cervical cancer (CC) treated by minimally invasive radical trachelectomy (MIRT) or abdominal radical trachelectomy (ART). The purpose of this multicenter study is to compare the oncologic and fertility outcomes of patients treated by MIRT or ART in a randomized controlled manner in China.

**Methods:**

This is a noninferiority, randomized controlled trial performed at 28 Chinese centers; the study is designed to compare the oncologic and fertility outcomes of patients treated by MIRT (robot-assisted or laparoscopic RT) or ART. Patients will be recruited if they have been diagnosed with stage IA1 (with lymphovascular space invasion), IA2, or IB1 CC (with a maximum tumor diameter ≤ 2 cm) in the FIGO 2009 staging system and histological subtypes of squamous carcinoma, adenocarcinoma, or adenosquamous carcinoma and if they are also aged 18 to 40 years. These candidates will be randomly assigned to undergo MIRT or ART. The primary endpoint will be disease-free survival. Secondary endpoints will consist of overall and disease-free survival rates, fertility outcomes, and quality of life. A total of 414 patients are needed to accomplish the study goal, with 90.1% power at a 0.050 significance level to detect an equivalence hazard ratio of 0.75 in the ART group, considering 20% loss to follow-up.

**Discussion:**

The results of the trial should provide robust evidence to surgeons regarding options for the surgical approach in patients with early-stage CC who have a strong willingness to preserve fertility.

**Trial registration:**

ClinicalTrials.gov NCT03739944. Registered on November 14, 2018

**Supplementary Information:**

The online version contains supplementary material available at 10.1186/s13063-020-04938-3.

## Background

With an estimated 570,000 new cases and 311,000 deaths in 2018 worldwide, cervical cancer (CC) ranks as the fourth most frequently diagnosed cancer and the fourth leading cause of cancer death in women [1]. The majority of CCs occur in low-income and middle-income countries. CC represents a major health challenge in China [2]. The standard surgical procedure for patients with early-stage CC is radical hysterectomy (RH) and pelvic lymphadenectomy. However, in the last two decades, with the widespread use of CC screening programs, there has been an increase in early-stage CCs diagnosed in women of childbearing age who desire childbearing. Therefore, fertility-sparing surgery (FSS), such as conization and radical trachelectomy (RT), has become one of the options for young women with early-stage CC.

Abdominal radical trachelectomy (ART) was first described by Romanian gynecologist E. Aburel in 1956 [3] and was “rediscovered” by the team of Smith and Ungár in the 1990s [4]. Vaginal RT, first performed by Daniel Dargent, involves resection of the cervix, the upper part of the vagina, and the proximal part of the parametria via a vaginal approach, combined with laparoscopic pelvic lymphadenectomy, while preserving the uterine corpus [5]. However, vaginal dissection in Dargent’s procedure must be performed by skilled surgeons. Furthermore, with the progress of minimally invasive technology, minimally invasive RT (MIRT) has allowed for a reduced length of hospital stay and estimated blood loss; decreased analgesic requirements, blood transfusion rates, and complication rates; earlier recovery of physiological functions; and improved esthetic outcomes [6].

A recent multicenter randomized controlled trial (RCT) [7] and a large cohort study [8] of minimally invasive versus abdominal RH for CC showed that the minimally invasive surgery (MIS) resulted in decreased survival compared with the laparotomic approach. The results of both studies aroused great controversy over the surgical approaches of CC worldwide. However, few data have been reported to evaluate the oncologic and/or fertility outcomes of RT with different surgical approaches, except for retrospective studies and systematic reviews. In a previously published paper from our center, ART versus vaginal RT yielded recurrence rates of 0 and 9.8% [9]. In a systematic review of stage IA to IIA CC, the recurrence rates after ART, laparoscopic RT, and robot-assisted RT were 4.7% (31/660), 6.3% (15/238), and 2.2% (2/89), respectively [10]. In another systematic review, among patients with abdominal, vaginal, laparoscopic, and robotic RT, the incidences of cervical stenosis were 11.0%, 8.1%, 9.3%, and 0%, respectively [11]. The lack of a prospective study promoted the conception of our RCT.

## Methods

### Design

The present investigation is a randomized, controlled, noninferiority, two-arm trial comparing the efficacy of different surgical approaches of RT on the oncology and fertility outcomes in Chinese patients with early-stage CC (Figs. 1 and 2). A total of 28 domestic centers will recruit 414 patients (207 per group) from December 31, 2018, to December 31, 2020. All the surgeries are to be performed by the specialists designated in the research center (the primary investigators are listed in Supplementary Table 1). The patients are randomized on the day of written consent obtainment by the random data website (http://random.your-data.cn:8095/random), which assigns each patient a randomization number. Specified surgeons from all centers are in charge of enrolling participants. When one potential eligible patient is enrolled, her information will be sent to [name], who will generate the allocation sequence and assign participants to interventions. The allocation, together with treatment information, will be discussed with the patient by her surgeons when patients attend the clinic to get results, and relevant informed consent will be signed. On the consent form, participants will be asked if they agree to the use of their data should they choose to withdraw from the trial. Participants will also be asked for permission for the research team to share relevant data with people from the universities taking part in the research or from regulatory authorities, where relevant. This trial does not involve collecting biological specimens for storage. Model consent form and other related documentation given to participants and authorized surrogates are available from the corresponding author on request.

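### The Design section gives two conflicting accounts of who randomises and of whether trial consent precedes allocation, so concealment is not assured and refusals after disclosure could go uncounted

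*Protocol article*

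**What the plan says.** The text is one paragraph of the Protocol article, under Methods, Design. It begins with a website: "The patients are randomized on the day of written consent obtainment by the random data website". What the site issues is a number: "which assigns each patient a randomization number".

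It then describes a route through people. Enrolment lies with the operators: "Specified surgeons from all centers are in charge of enrolling participants". Allocation is given to someone else: "When one potential eligible patient is enrolled, her information will be sent to" one named individual, "who will generate the allocation sequence and assign participants to interventions". Disclosure comes next: "The allocation, together with treatment information, will be discussed with the patient by her surgeons when patients attend the clinic to get results". Only at the end of that sentence does the signature appear: "and relevant informed consent will be signed". The text then turns to what the form contains: "On the consent form, participants will be asked if they agree to the use of their data should they choose to withdraw from the trial".

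Two other sections bear on this:

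- Data management keeps women who consent and then refuse their arm in follow-up, and analyses them by intention to treat. Data from women who leave early may be used unless they objected when signing. After withdrawal of consent, data may be used only with the woman's written statement that she does not object.
- The section on parameters for assessing efficacy endpoints states that patients and surgeons know the operation and that only those analysing the data are blinded.

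**The concern.** Randomisation protects the comparison under two conditions: the assignment cannot be influenced by knowledge of the patient, and membership of the trial is settled before the arm is known. The second account leaves both open. Someone who holds a patient's details and also produces the sequence could, even unintentionally, fit one to the other. A woman who hears her arm before signing can decline because of it.

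An intention-to-treat analysis cannot recover women who never enter the dataset. Refusal that depends on the arm is plausible here. The Background reports worse survival after minimally invasive hysterectomy in a randomised trial and a cohort study, and controversy that followed. It also lists shorter stay, less blood loss and better cosmetic results for the minimally invasive operation, so the direction of any such refusal cannot be predicted.

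**Working it through.** The plan gives no figure on this point to reproduce. The check is a comparison of the sentences.

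| Question | Website account (Design, opening) | Person account (Design, later sentences) |
|---|---|---|
| Who or what randomises? | The website, which issues a number | One person, who generates the sequence and assigns |
| What does the allocator hold beforehand? | Not stated | The patient's information |
| When does allocation happen? | On the day written consent is obtained | After enrolment, before the clinic discussion |
| When is consent signed? | Same day as randomisation | Mentioned only after the allocation has been discussed |

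1. **Who randomises.** The two accounts could be reconciled if the person merely operates the website. The text does not say so. It gives the person both sequence generation and assignment, and gives the website only the issue of a randomisation number. It mentions no sequence prepared in advance and no locking of eligibility before assignment.

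2. **Order of consent and allocation.** The opening sentence puts consent and randomisation on the same day, most naturally with consent first. The later sentences run: enrolment, information sent, assignment, discussion of the allocation, signature.

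3. **Which consent.** The adjective relevant leaves this open. The next sentence, on use of data after withdrawal from the trial, is trial-consent content, so trial consent is the natural reading. On that reading the woman also answers the data-use question after learning her arm, and Data management makes later use of her data depend on that answer.

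4. **Who is counted.** The intention-to-treat rule in Data management has two conditions: the woman has consented to take part, and she then departs from her allocation. A woman who is assigned, hears her arm and does not sign fails the first condition. No other statement in the article counts her.

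5. **Size.** The loss in each arm would be 207 multiplied by that arm's proportion refusing after disclosure. The 207 per group is in the Design section; the two proportions are nowhere in the article. Any resulting bias would also need the recurrence risk of those who refuse, which is not given either. No magnitude follows.

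**The case against.** The strongest defence has three parts.

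**Concealment may be intact.** Surgeons enrol, a different person allocates, and enrolment comes first. A central allocator remote from the enrolling surgeon is compatible with concealment, and that person may simply run the website. The clause on generating and assigning can be read as a description of roles, not as a time order for each patient. A reader might infer from the paragraph that allocation is not concealed. The documents do not support that. The absence of blinding does not establish it either, since blinding and concealment are separate matters.

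**The later signature may be operative consent.** It follows mention of treatment information, and the efficacy-endpoints section links explanation of the operation and its risks to signing consent. Data management speaks of women who consent and then refuse their allocation, which presupposes trial consent before the arm is known. So it cannot be said that trial consent is taken after allocation, only that the text points both ways.

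**The article is a condensed source.** The flow and SPIRIT figures are not shown, and the full protocol may set out the order.

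These points limit the conclusion but do not remove it. The article does not leave the procedure out. It states it in two ways that do not agree, and a site following the later sentences literally would disclose the arm before obtaining a signature on a form with trial-consent content.

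**Conclusion.** The point holds as an internal contradiction with a practical consequence. The Design section disagrees with itself on who or what randomises and on whether trial consent precedes allocation. If the second account is the one followed, concealment is not assured, and refusal after disclosure is possible and falls outside the intention-to-treat rule. This rests on reading the later signature as trial consent. That is the more natural reading but not the only one.

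No size is claimed. A reader might infer that two or three higher-risk women moving between arms would shift the hazard ratio by 20% to 30%, since about 10 recurrences per arm are expected (207 × 5% = 10.4). That treats women as recurrences. Suppose, purely as an assumption, that higher-risk women recur at 20% and others at 5%. Exchanging three of them changes the expected count in one arm by 3 × (0.20 − 0.05) = 0.45 events, or about 4% of 10.4. The documents give neither these risks nor any number of refusals, so no figure of this kind can be defended.

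**What to change.** State one order and use it throughout:

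1. Eligibility is confirmed and trial consent signed.
2. The patient is registered on the website.
3. The website releases the next assignment from a concealed sequence generated in advance.
4. The surgeon discloses the arm and obtains operative consent.

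Remove the route in which a person holding patient information generates the sequence. Define the intention-to-treat set as every randomised woman, subject to her consent to data use.

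For women already allocated, reconcile the website or allocator log with the list of enrolled patients, and report by arm how many were allocated but never consented. Checking consent dates among enrolled women is not enough, because it cannot find those who never signed. If only some women consented after allocation, keep them in the main analysis and add a sensitivity analysis without them. If late consent was the practice at every site, that analysis would have almost nobody left, and the order should simply be reported as a limitation.

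The Design section plans recruitment to end on December 31, 2020. If it has closed, the change of workflow comes too late, but the clarification and the log reconciliation can still be done.

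The cost is small: a protocol amendment, a workflow instruction to sites and one log reconciliation. The website already exists.

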**Fig. 1 Fig1:**
[figure not shown]
CONSORT flow diagram of the study. ARH, abdominal radical hysterectomy; MIRT, minimally invasive radical trachelectomy; ART, abdominal radical trachelectomy

**Fig. 2 Fig2:**
[figure not shown]
SPIRIT figure of the study

Figure 1 refers to the CONSORT flow diagram. Survival outcomes (disease-free survival [DFS] and overall survival [OS]) will be analyzed comprehensively, as well as the fertility and pregnancy outcomes and quality of life (QoL).

Any important protocol modifications, happened before or during the trial, will receive a deliberative evaluation by the primary investigator and be approved by the plenary session consisting of all participating centers. Once the modifications were approved, a copy will be sent to the funders and all centers. The clinical trial registry will be updated due to the modifications. Any deviations from the protocol will be fully documented using a breach report form.

#### Inclusion criteria

Inclusion criteria are as follows: patients with International Federation of Gynecology and Obstetrics (FIGO) 2009 stage IA1 with lymphovascular space invasion (LVSI), IA2, or IB1 with tumor size ≤ 2 cm CC; no evidence of upper endocervical involvement (tumor confined to the cervix as proved by preoperative imaging, and a cranial extent of the tumor that is at least 1 cm away from the internal os); no lymph node spread or distant metastasis; histological subtype of squamous cell carcinoma, adenocarcinoma, or adenosquamous carcinoma; aged 18 to 40 years; ability to provide fully informed written consent for participation in this study; strong desire to preserve fertility and no history of fertility impairment; ability to undergo long-term follow-up after surgery; and Eastern Cooperative Oncology Group (ECOG) performance status [12] of 0 to 1.

#### Exclusion criteria

The exclusion criteria were as follows: histological subtype of neuroendocrine, clear cell, and serous cell type or metastatic carcinoma; clinically advanced disease (IB1 with tumor size > 2 cm or stages IB2 to IV); current pregnancy; age younger than 18 or older than 40 years; having received neoadjuvant chemotherapy or radiotherapy; without a systematic preoperative imaging evaluation (pelvic MRI with or without PET/CT); unwillingness to participate in this study; and preexisting malignancy, severe systemic disease or severe mental illness.

### Main objective and primary endpoint

The primary objective of the analysis is to evaluate the 5-year DFS related to different surgical approaches for radical trachelectomy (RT). The primary endpoint will be recurrence confirmed by imaging or histology.

### Secondary objectives and secondary endpoints

The secondary objectives are as follows:
To evaluate the OS at the 5-year follow-upTo assess different strategies of RT in terms of fertility and obstetric outcomesTo compare the incidence of perioperative complications of different surgical approachesTo compare major perioperative complications within 28 days after surgery and major postoperative complicationsTo determine the general and specific QoL

Secondary endpoints will therefore be the following:
All-cause mortalityFertility outcomes consisting of cervical incompetence, natural pregnancy, and infertility treatment such as intrauterine insemination or IVF-ET; obstetric outcomes consisting of the time interval between the RT surgery and pregnancy; the overall mean length of time during which conception was attempted; the number of pregnancies; the mode of delivery; and the outcome of each pregnancy, such as spontaneous abortion, induced abortion, drug abortion, preterm birth, premature rupture of membranes, fetal growth restriction, and full-term birthPerioperative complications consisting of injury of the ureter, bladder, bowel, blood vessels, or nerves, and vaginal bleeding, and postoperative complications consisting of postoperative pelvic infection, pelvic lymphocele, intrauterine infection, Asherman syndrome, abnormal menstruation, urinary tract infection, hydronephrosis, intestinal obstruction, chronic pain, varices at the site of uterovaginal anastomosis, and fistula formationMajor perioperative and postoperative complications consisting of early postoperative complications (cerebrovascular, pulmonary, and renal diseases; ileus; abdominal wound complications; septicemia; thromboembolism; and lymphocele formation and secondary infection) and delayed postoperative complications (lymphedema, vaginal evisceration)QoL assessment comprising the authorized Chinese edition of EORTC QLQ-C30 [13] and its CC module QLQ-CX24 [14], the 19-item Female Sexual Function Index (FSFI) [15], and the PFIQ-7 questionnaire [16].

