### Data management

All medical information required according to the protocol will be collected via the case report forms based on the website, facilitating the real-time, central assessment of the data completeness and patient follow-up. This information will include demographic data, the surgical approach, the skin-to-skin operative time, EBL, and the surgical energy devices. The pathogenic material will also be collected, including the results regarding the tumor histology subtype, FIGO stage, grade (well, moderately or poorly differentiated), tumor size, depth of stromal invasion, LVSI, lymph node status, and surgical margin status. After RT, data on surgical complications, bladder/intestinal function recovery, QoL, fertility and obstetrics outcomes, and disease recurrence and survival information will also be followed.

The questionnaires will be completed, the ovarian reserve function will be evaluated, and a urodynamic study (UDS) and anorectal manometry will be assessed within 4 weeks before surgery, at 4 months postoperatively, at 12 months postoperatively, and then once a year thereafter. After the RT (Table 1), the patients will be required to attend the customed follow-up regularly, at 3- to 6-month intervals in the first 2 years after completing the treatment, 6- to 12-month intervals from the third to the fifth year after treatment, and then at 1-year intervals thereafter. The effects of the follow-up scheme (pelvic examination, the ThinPrep cytological test and/or human papillomavirus testing, transvaginal ultrasonography, an abdominal ultrasound scan, chest radiography, and serum tumor marker, i.e., squamous cell carcinoma and Ca125) will be evaluated at each visit.

**Table 1 Tab1:** Lists of clinical assessments at different time points

Check-up time	Inspection items	Documentors	Directors
Within 4 weeks before RT	Urodynamic assessment	CRF	Research centers
	Anorectal manometry	CRF	
	QoL assessment	CRF	
	Sexual function scale	CRF	
	Ovarian reserve function	CRF	
Ten to 14 days after RT	Operation details	CRF	Research centers
	Residual urine	CRF	
	Perioperative complications	CRF	
Four weeks after RT	Postoperative complications	CRF	
	Pathological report	CRF	
Four months after RT	Urodynamic assessment	CRF	Research centers
	Anorectal manometry	CRF	
	QoL assessment	CRF	
	Ovarian reserve function	CRF	
	Postoperative adjuvant therapy	CRF	
	Data curation	Database	Main center
Every 12 months after RT	Urodynamic assessment	CRF	Research centers

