	Anorectal manometry	CRF	
	QoL assessment	CRF	
	Sexual function scale	CRF	
	Ovarian reserve function	CRF	
	Pregnant desires and outcomes	CRF	
	Survival outcome	CRF	
	Data curation	Database	Main center
	Follow-up time, scheme, and results	Database	

*CRF* case report form, *QoL* quality of life, *RT* radical trachelectomy

This trial will be conducted in compliance with the current version of the protocol, with all statutory and regulatory requirements. The Data Safety Monitoring Committee (Supplementary Table 2) will regularly receive study data, including complications, patient conditions, and survival outcomes. This committee will be composed of physicians, administration staff, and scientific researchers, who are not participating in the study as investigators and who will be provided with available collected data during the study. The committee reserves the right to terminate the study at any time for medical or administrative reasons. In the case of loss to follow-up, the surgeons or investigators will do their best to contact each patient involved to identify if he/she is alive. If an individual leaves the research study prematurely, data related to the participant can still be used unless an objection was recorded when the patient signed the consent form. If consent is withdrawn, no data about the individual may be used unless the patient states in writing that he/she does not object.

For participants who consent to participate the trial but deviate from intervention protocols, i.e., refuse the randomized allocation, the surgical and follow-up data will still be collected the same as participants following the protocol, which will be analyzed according to intention to treat.

The trial results will be communicated to the funders, investigators, and other relevant groups via publications, reporting results in databases, data sharing arrangements, and social media (WeChat).

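### No listed fertility endpoint captures fertility lost after randomisation, and the pregnancy outcomes have no fixed denominator

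*Protocol article*

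**What the plan says.** The abstract and the Design section name oncologic and fertility outcomes together as the object of comparison. The inclusion criteria require "strong desire to preserve fertility and no history of fertility impairment".

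The section on secondary objectives and endpoints introduces its lists as what the outcomes consist of. Fertility outcomes are cervical incompetence, natural pregnancy and infertility treatment. Obstetric outcomes are the interval from surgery to pregnancy, "the overall mean length of time during which conception was attempted", and "the number of pregnancies; the mode of delivery; and the outcome of each pregnancy". Neither these lists nor the complication lists contain fertility retained, uterus retained or adjuvant therapy.

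The Data management section and Table 1 collect relevant data:
- "Postoperative adjuvant therapy" at four months.
- Pathology, including "LVSI, lymph node status, and surgical margin status".
- Ovarian reserve before surgery, at 4 and 12 months, and yearly: "the ovarian reserve function will be evaluated".
- "Pregnant desires and outcomes" every 12 months.

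The Statistics section assigns the t test to continuous variables and Kaplan-Meier plots to recurrence and death. It names intention to treat and per protocol for the survival outcomes. Separately, Data management says that women who depart from the allocated intervention are followed in the same way and analysed by intention to treat.

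**The concern.** A woman is randomised on the day she consents. Nodal and margin status become known at or after surgery, and some women may then receive further treatment. If that treatment, or anything else after randomisation, ends her ability to conceive, no listed endpoint records it as an outcome.

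She contributes nothing to time to pregnancy, mode of delivery or the outcome of each pregnancy. Comparing arms on those items compares subgroups formed after randomisation, and randomisation no longer protects the comparison.

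The article says that blinding of surgeons and treating clinicians was not feasible, so the use of adjuvant therapy could differ by arm. If it did, it might also affect DFS, and any cost in fertility would have no endpoint of its own. At stake is whether the trial can answer the fertility part of its stated question.

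**Working it through.** The documents give no rate of fertility loss, adjuvant therapy or pregnancy, so there is no plan figure to reproduce. The check has two parts.

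**1. Endpoint by endpoint: what does a woman who lost fertility contribute?**

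| Listed outcome | Contribution |
|---|---|
| Interval from surgery to pregnancy | None; a t test needs an observed interval |
| Time attempting conception | None after the loss |
| Mode of delivery, outcome of each pregnancy | None |
| Natural pregnancy, number of pregnancies | Zero if all randomised women are the denominator; none if restricted |
| Cervical incompetence, infertility treatment | Do not measure loss of fertility |

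Only the fourth row can register the loss, and it depends on a denominator that the article does not state.

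**2. How well would pregnancy register the loss?**

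Inputs: n = 207 per arm (Design section). Assumed: the share L losing fertility in each arm, and the share p conceiving among women who keep it, equal in both arms.

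- Pregnancy rate per woman who kept fertility = p, identical in both arms whatever the loss.
- Pregnancy rate per randomised woman = p × (1 − L).
- Power, two-sided 0.05 = Φ[(|p₁ − p₂| − 1.96·SE₀)/SE₁], where SE₀ = √(2p̄(1 − p̄)/n) and SE₁ = √([p₁(1 − p₁) + p₂(1 − p₂)]/n).

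Worked case, L = 10% v 20% and p = 40%:

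- Per woman who kept fertility: 40% v 40%.
- Per randomised woman: 0.40 × 0.90 = 36% v 0.40 × 0.80 = 32%. That is 207 × 0.36 ≈ 75 v 207 × 0.32 ≈ 66 women.
- Power on pregnancy per randomised woman: SE₀ = 0.0466, SE₁ = 0.0465; (0.04 − 0.0913)/0.0465 = −1.10; Φ = 0.135, about 14%.
- Power on the loss itself: SE₀ = 0.0351, SE₁ = 0.0348; (0.10 − 0.0688)/0.0348 = 0.90; Φ = 0.815, about 82%.

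Other assumed rates:

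| Loss | p | Per randomised woman | Women pregnant | Power, pregnancy | Power, loss |
|---|---|---|---|---|---|
| 10% v 15% | 40% | 36% v 34% | 75 v 70 | 6% | 34% |
| 10% v 20% | 40% | 36% v 32% | 75 v 66 | 14% | 82% |
| 5% v 15% | 50% | 47.5% v 42.5% | 98 v 88 | 17% | 93% |

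Over a wider grid (loss from 5% v 10% to 10% v 30%, p of 30% and 50%), power is 5% to 55% on pregnancy per randomised woman and 49% to 99.9% on the loss. All these powers assume complete data on 207 women per arm. The plan allows for 20% loss to follow-up, which would lower them.

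**The case against.** A reader might infer that an arm preserving fertility in fewer women could look equal on every listed fertility outcome. The documents do not support that. Natural pregnancy and number of pregnancies carry no restriction to women who can still conceive. Because every woman enters wishing to preserve fertility, all randomised women are a natural denominator, and the intention-to-treat sentence in Data management is not confined to survival. Counted that way, the worked case gives about 75 v 66 women, which is a visible difference. This part of the objection stands and limits the point: such counts register the loss, but weakly.

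Three further readings also go too far:

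- **Hysterectomy after randomisation.** The only trace of hysterectomy within the trial is "ARH, abdominal radical hysterectomy" in the Fig. 1 caption. The figure is not shown, so it is unknown whether that box lies before or after randomisation. The adjuvant-therapy item in Table 1 is sufficient without it.
- **Birth outcomes are missing.** Preterm and full-term birth are listed as examples of pregnancy outcomes. Only a live-birth summary per randomised woman is absent.
- **Adjuvant therapy differs by arm, or always ends fertility.** The documents say neither.

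It can also be said that denominators for secondary endpoints belong in a full protocol or SAP, neither of which is shown. That is fair for the denominator alone, which is therefore not the core of the point. The choice of endpoints is the protocol's task, this list is worded as complete, and the article itself states the methods that would leave non-conceivers out of the time-to-pregnancy comparison.

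**Conclusion.** The point holds in a limited form. The closed list has no endpoint for fertility retained or lost, although fertility is a stated aim and adjuvant therapy is foreseen. Followed as written, the t test on time from surgery to pregnancy conditions on having conceived, and the delivery and per-pregnancy items do so by nature. Pregnancy counts over all randomised women are a weak substitute: about 14% power against about 82% for a direct endpoint at an assumed 10% v 20% loss.

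The size rests wholly on assumed rates. If the arms hardly differ in loss, the practical effect is small. The gap in the endpoint list itself does not depend on those assumptions. These are secondary endpoints, so the primary DFS comparison is not invalidated. The change is worth making because it is cheap and bears directly on the trial's fertility question.

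**What to change.** 1. Add a secondary endpoint, fertility retained, with all randomised women as denominator. Derive it from operation details, the four-month adjuvant-therapy item and ovarian reserve. The investigators should define in advance, without knowledge of results by arm, which events count as loss. The definition should not simply equate any adjuvant therapy with loss.
2. Make pregnancy and at least one live birth, each per randomised woman, the leading fertility comparison.
3. Replace the t test on time to pregnancy with cumulative incidence over all randomised women.
4. Report adjuvant therapy by arm beside DFS.
5. Label mode of delivery and the outcome of each pregnancy as descriptive.

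Cost: endpoint wording and a few derived variables, mostly from data already collected. Table 1 has no explicit item for uterine retention or a later hysterectomy, and preterm or full-term birth does not by itself record a live birth, so one or two form items may be needed. Rates per randomised woman will be lower than clinicians are used to and will include women who never try to conceive. The pregnancy and birth comparisons will still have low power for modest differences and should be reported as estimates with confidence intervals.
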